### Study assessment

The study was approved by the “East III” ethical committee (IDRCB: 2019-A03332-55). Clinicians will inform all patients enrolled in the study that their biological samples could be used for research purposes and patients will express their non-opposition. All donors participating may object at any time, leading to the prompt disposal of their tissue and any derived material, as well as the cessation of data collection. The enrollment period of the study will be 3 years, each patient will be monitored for 5 years and study length will be 10 years.

#### Collection of tumor and blood samples

Blood samples will be collected before surgery as part of regular medical care. No blood draw will be done specifically for this study. An additional volume of blood will be collected in two 5 ml serum separator tubes and seven 5 ml EDTA tubes and transported to the laboratories to be processed.

Tumor samples will be collected during surgery as part of regular medical care and sent to the pathology laboratory. The surplus tissue (including tumor and adjacent normal tissues) not required for diagnosis will be transported to the laboratory in vials containing medium supplemented in antibiotics and ROCK inhibitor Y-27632.

#### Sample processing

##### Serum preparation

Serum will be isolated by a two-step centrifugation (2500 g, 10 min, RT), and aliquoted (about 5 tubes of 300 μL) before storage at − 80 °C.

##### Isolation of Peripheral Blood Mononuclear Cells (PBMC)

PBMC will be isolated from human peripheral blood by density gradient centrifugation using Ficoll-Paque in Leucosep tubes. Then, cells will be resuspended in cold Fetal Bovine Serum (FBS), and counted. PBMC will be resuspended in freezing solution (10% DMSO, 90% non-inactivated FBS), aliquoted (about 5 cryovials, 4.10^6^ cells/cryovial), and frozen with gradually decreasing temperatures (1 °C/min) to − 80 °C before long-term storage at liquid nitrogen temperatures in stored in the Biological Resource Center ‘Tumorotheque de Caen Basse-Normandie’ (NF-S 96900 quality management, AFNOR No. 2016: 72860.5).

##### Tumor sample

Tumor specimen will be cut into 1-3 mm^3^ pieces. Depending on the quantity of tumor, different procedures will be carried out in the following order of priority: 1) one random piece will be processed for the isolation of viable cells and PDTO establishment; 2) two random pieces will be snap frozen and stored at − 80 °C for molecular analyses; 3) One random piece will be fixed in paraformaldehyde for paraffin embedding and subsequent histopathological analysis and immunohistochemistry; 4) the remainder will be cryopreserved in freezing solution (10% DMSO, 90% non-inactivated FBS) for future isolation of viable cells. All tumor samples will be stored in the Biological Resource Center ‘Tumorotheque de Caen Basse-Normandie’.

#### Medical data collection

Medical data collected for each patient in order to correlate biological data (including PDTO response to treatment) with clinical response are indicated in Table 2.

**Table 2 Tab2:** Medical data collected for each patient

Clinical parameters	Age, sex, weight, height, ECOG performance status, Exposure to tobacco and alcohol, Cancer location and TNM-8 classification
Histological diagnosis	Type, squamous differentiation, keratinization type, p16 status
Biologic parameters	Serum neutrophils, albumin and leukocytes levels
Pathological pronostic factors	Surgical margin, lymph node metastasis with or without capsular rupture, vascular or lymphatic embolization, perineural invasion
Oncologic treatments	Radiotherapy (volume, dose, fraction) Chemotherapy (molecules, administration regimen)
Response to treatment	Disease-free survival, Progression-free survival, Overall survival.

#### Establishment of panel of PDTO

Tumor pieces will be dissociated enzymatically and mechanically to obtain isolated cells or small cell clusters (Fig. 2). Cells will be embedded in an extracellular matrix (growth factor-reduced Matrigel or BME II) and cultured in a medium supplemented with growth factors and signal pathway inhibitors [Advanced DMEM (Gibco) supplemented with 100 UI/mL of penicillin and streptomycin (Gibco), 1% GlutaMAX (Gibco), 1X B27 (Gibco), 1.25 mM NAC (Sigma-Aldrich), 50 ng/mL EGF (PeproTech), 10 ng/mL FGF-10 (PeproTech), 5 ng/mL FGF-b (PeproTech), 500 nM A-83-01 (PeproTech), 10 μM Y27632 (Interchim), 10 mM Nicotinamide (Sigma-Aldrich), 1 μM PGE2 (PeproTech), 1 μM Forskolin (Peprotech), 0.3 μM CHIR99021 (Biogems), 100 μg/mL Primocin (InvivoGen), 50% Wnt3a, RSPO3, Noggin-conditioned media (L-WRN, ATCC), and 10% RSPO1-conditioned media (Cultrex HA-R-Spondin-1-Fc 293 T, Amsbio)]. Culture medium will be changed twice a week. Once formed, PDTO will be dissociated and reseeded to amplify them for experimental purposes. Cryovials will be prepared at regular intervals by dissociating and resuspending PDTO in Recovery Cell Culture Freezing Medium (Gibco) prior to be biobanked in liquid nitrogen. It should be noted that PDTO line will be considered as established when it will be maintained for more than 3 passages. For each PDTO line, samples will be kept frozen for DNA/RNA/protein analysis and others will be embedded in paraffin for histopathological analysis. This will allow comparisons between the characteristics of the PDTO and the tumor from which they are derived in order to validate their correspondence.

**Fig. 2 Fig2:**
[figure not shown]
Establishment and characterization of PDTO derived from HNSCC and evaluation of response to treatments to assess its predictive value

#### Coculture of PDTO with immune cells

Co-culture of PDTO and autologous immune cells will be based on the protocol described by Cattaneo et al. [21] Briefly, PDTO specific T cells will be induced through serial co-culture with dissociated PDTO. PBMC (~ 10.10^6^ cells) will be thawed and set to resting condition with IL-2 (150 U/mL) overnight. Meanwhile, PDTO will be treated with IFNγ (200 ng/mL) for 24 hours to favor antigen presentation and will be dissociated to produce Antigen Presenting Tumor Cells (~ 0.5.10^6^ cells APTC). PBMC and APTC will be next co-cultured (20:1 ratio) in a CD28 (5 μg/mL) coated culture plate for successive periods of 7 days to induce clonal expansion of PDTO specific T cells. T cells will be then evaluated for their tumor reactivity through the detection of activation (CD137) and functional (CD107a, IFNγ) markers by flow cytometry (Cytoflex, Beckman Coulter) and will be cryopreserved for later use for the evaluation or response to treatments.

#### Evaluation of response to treatments

The evaluation of the response to treatments will be performed when PDTO have reached a diameter of 150 μm in « PDTO treatment medium », corresponding to the PDTO culture medium lacking N-Acetylcysteine, Y-27632 and primocin.

PDTO will be collected, resuspended in 2% extracellular matrix/PDTO culture medium and then platted in white and clear bottom 96-well plates previously coated with a 1:1 volume mix of PDTO treatment medium with extracellular matrix. In the case of evaluation of the response to radiotherapy, PDTO will be before irradiated using the CellRad System (FAXITRON Bioptics). In the case of evaluation of the response to chemotherapy or PARP inhibitors, drugs are prepared in 2% extracellular matrix/PDTO culture medium and added 1 hour after PDTO have been plated.

In the case of evaluation of the response to immunotherapies, PDTO will be co-cultured with PDTO specific T cells previously generated (*see co-culture of PDTO with immune cells*) at a 5:1 ratio. Treatments (such as Nivolumab or Pembrolizumab) will be added directly in the co-culture. A condition containing an MHC-I blocking antibody will be added to control for antigen specific killing.

PDTO morphology will be monitored by taking images during the required time using Incucyte S3 (Sartorius). At the endpoint, PDTO response will be assessed using CellTiter-Glo 3D cell viability assay (Promega) according to the manufacturer’s instruction and luminescence will be measured using GloMax Discover GM3000 (Promega) with the associated software. Results will be normalized to the control condition. IC50 will be calculated with GraphPad software. The ability of T cells to recognize and induce lysis of PDTO will be monitored via analysis of caspase 3 cleavage within PDTO and visualization of LAMP-1 on the membrane of CD8+ T cells.

The treatment response of the PDTO will be finally compared to the clinical response (PFS/DFS/OS) of the patient from whom they are derived in order to validate the predictive value of this model for HNSCC.

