## Background

### Head and neck squamous cell carcinoma (HNSCC) and treatment modalities

HNSCC is the sixth most common cancer worldwide, with 890,000 new cases and 450,000 deaths in 2018 [1]. It is estimated that locoregional control can be achieved in half of the cases, in part because 65% of patients are diagnosed at advanced stages (T3T4) and also because locoregional relapse is frequent. The prognosis of HNSCC is poor with a 5-year survival rate for all stages around 55% [1].

Treatment of HNSCC is based on several modalities. Surgery is chosen when a total excision is possible. Radiotherapy may be proposed as primary treatment or as adjuvant treatment depending on the existence of poor prognostic factors (margin status, capsular rupture, advanced tumors, etc.) [2]. Systemic treatments such as chemotherapy (cisplatin) or targeted therapy (cetuximab) can be used in combination with radiotherapy. At the recurrent or metastatic phase, HNSCC are often treated with systemic treatments. Immunotherapy has also entered the therapeutic arsenal for HNSCC with the use of anti-PD1 (programmed death-1) agents Nivolumab or Pembrolizumab [1].

The prognosis of HNSCC is burdened by radioresistance, which is partly due to hypoxia and proliferation among other reasons. This explains the lack of effectiveness of radiotherapy in many cases. Research is thus focused on mechanisms factors of radioresistance. Among them, genomic instability of DNA repair systems plays an important role [3]. Molecules affecting DNA repair systems are currently being studied such as PARP inhibitors like Olaparib which was FDA-approved in 2014 since they could allow sensitization of tumor cells to radiotherapy [4]. Another promising field of research is the use of different particles such as proton beam therapy. It has two major advantages over X-rays: more precise energy delivery to the tumor and fewer side effects on surrounding healthy tissues [5].

Patients with HNSCC suffer from numerous complications of treatment. The side effects are increased by therapeutic combinations. These treatments can alter breathing, phonation and swallowing because of the tissue changes caused by the radiation in the areas surrounding the tumor. Patients’ quality of life is altered by functional disorders and by the social impact of treatments. Predicting tumor response and tissue effects from innovative combinations has the potential to improve the therapeutic index.

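### Endpoint viability relative to control can mix sensitivity with growth rate when treatment acts on division, and no start-of-treatment value is stated that would separate the two

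*Protocol article*

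**What the plan says.** The metric is set in the protocol article, *Evaluation of response to treatments*. The assay starts at a common size ("The evaluation of the response to treatments will be performed when PDTO have reached a diameter of 150" μm). The read-out is a single one: "At the endpoint, PDTO response will be assessed using CellTiter-Glo 3D cell viability assay". The reduction to a score is: "Results will be normalized to the control condition. IC50 will be calculated with GraphPad software".

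Images are taken over time, but their stated purpose is morphology: "PDTO morphology will be monitored by taking images during the required time using Incucyte S3". Assay length is not tied to doubling time. Caspase 3 and LAMP-1 are added read-outs for the T-cell assay only.

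The same section then sets PDTO response against each patient's PFS, DFS and OS to validate the model. *Statistical analyses* plans a Chi2 test and Cohen's kappa for that comparison, and ROC curves and logistic regression for predictive factors. No growth term is mentioned. The Background section on HNSCC and treatment modalities says that prognosis is burdened by "radioresistance, which is partly due to hypoxia and proliferation among other reasons".

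**The concern.** Dividing the treated signal by the control signal at the end of the assay removes starting cell number. It does not remove the number of divisions that the control completed, and that number differs between patients' lines. A common starting diameter standardises size, not doubling time. With no time-0 value, slowed growth and cell killing cannot be told apart.

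Where treatment acts on division, fast lines then look more sensitive than slow lines that respond equally. The Background names proliferation as a partial cause of radioresistance. On that premise a fast-growing tumour may do worse in the patient while its organoids look more sensitive, so the artefact could weaken, or even reverse, the association being tested. At stake are secondary objectives ii (predictive value for chemotherapy and radiotherapy) and v (molecular signatures of response).

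**Working it through.** The plan gives no figure on this point, so there is none to reproduce.

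**Inputs.** From the article: one endpoint reading, control as denominator, IC50 as summary. Not given, so assumed: assay length T (6 days in the lead example; 5, 7 and 10 days for the range), doubling time Td (1.5 to 10 days), exponential growth, and the type of effect. With starting signal x0, the control ends at x0·2^(T/Td). The score is V = treated/control.

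**1. Division rate halved.** V = 2^(T/2Td) / 2^(T/Td) = 2^(−T/2Td).
- T = 6, Td = 2: 2^1.5 / 2^3 = 2.83/8 = 0.354.
- T = 6, Td = 6: 2^0.5 / 2^1 = 1.41/2 = 0.707.
- T = 7: V = 0.20, 0.30, 0.45, 0.62, 0.71 and 0.79 for Td = 1.5, 2, 3, 5, 7 and 10 days.

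**2. Complete arrest.** V = 2^(−T/Td). If T/Td ≤ 1, V cannot fall below 0.50. At T = 7, V = 0.09 (Td 2), 0.50 (Td 7) and 0.62 (Td 10).

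**3. IC50 at equal potency.** The growth-rate-corrected response is GR = 2^[log2(x/x0)/log2(control/x0)] − 1, where 1 means no effect and 0 means full arrest. Let GR = 1/(1+c), with c the dose in units of true potency. Then V = [(1+GR)/2]^(T/Td). Setting V = 0.5 gives GR = 2^(1−Td/T) − 1 and IC50 = 1/GR − 1:

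| Td (days) | 1.5 | 2 | 3 | 5 | 7 | 10 |
|---|---|---|---|---|---|---|
| T = 5 | 0.60 | 0.94 | 2.13 | none | none | none |
| T = 7 | 0.38 | 0.56 | 1.06 | 3.57 | none | none |
| T = 10 | 0.25 | 0.35 | 0.60 | 1.41 | 3.33 | none |

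At T = 7, IC50 shifts 3.57/0.38 ≈ 9-fold between Td 1.5 and Td 5 at identical potency. If the maximum effect includes net cell loss (GR falling to −0.5), IC50 at T = 7 exists for every line but still runs from 0.23 (Td 1.5) through 1.09 (Td 5) to 5.17 (Td 10).

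**4. Cells lose division but stay ATP-positive** (possible after irradiation). For fraction f, V = (1−f) + f·2^(−T/Td). With f = 0.8 and T = 7: 0.2 + 0.8 × 0.088 = 0.27 (Td 2), against 0.2 + 0.8 × 0.5 = 0.60 (Td 7).

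**5. Pure killing.** A fraction f killed at the start gives V = 1 − f. A constant kill rate k gives V = exp(−kT). Neither contains Td, so there is no growth bias.

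**6. How the corrected score behaves.**
- In case 1 with T = 6: 2^(1.5/3) − 1 = 2^(0.5/1) − 1 = 0.414 in both lines.
- With half the cells killed at the start, the fast line has control 8 and treated 4, the slow line control 2 and treated 1. V = 0.50 in both, but GR = 2^(2/3) − 1 = 0.59 against 2^0 − 1 = 0.00.
- In a slow line it is fragile. With control growth of 1.41-fold, growth halved by treatment (1.19-fold) and x0 misread by +10% or −10%, GR moves from 0.41 to 0.24 or 0.53.

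**The case against.** The strongest reply is that the artefact is conditional. Under a fixed initial kill or a constant kill rate, endpoint viability is free of growth bias and it is the growth-corrected score that depends on doubling time. The article does not show which effect model applies to its treatments. This stands. It rules out saying that slow lines are called resistant whatever their true sensitivity, and it rules out replacing IC50 with GR as the main measure.

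Second, the article is condensed: time-0 wells, assay length and image quantification may be in the full protocol or laboratory procedures. That is fair, and no contradiction or wrong figure is alleged. But read-out, denominator and summary are stated, and the concern is with that stated combination. If a time-0 value is already taken, the remedy is mostly a matter of using it.

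Third, a reader might infer that proliferation drives outcome. The Background says only that it is one partial cause of radioresistance, and nothing states that doubling time in culture tracks proliferation in the tumour. Weakening or reversal of the association is therefore possible, not shown. The same holds for proliferation genes entering the signatures.

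Fourth, objective iii (radiosensitization by a PARP inhibitor) can be assessed within a line, with and without the inhibitor. Growth differences between lines do not confound that contrast, though they can affect how its size compares across lines.

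**Conclusion.** The concern holds in a conditional form. For effects that act on division, the stated score depends on each line's doubling time, and nothing stated in the article detects or corrects this. In the lead example equal effects read 35% and 71% of control. At T = 7 days the range is 20% to 79%, and equal potencies give IC50 values about 9-fold apart or no IC50 at all. All of these rest on assumed assay lengths, doubling times and effect types, so they show that the bias can be large, not how large it is here.

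The consequence is limited to objectives ii and v. The establishment rate and its sample size are unaffected. The change is worth making because a time-0 value that was not captured cannot be recovered later.

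**What to change.** In *Evaluation of response to treatments*:
- Quantify PDTO area or volume from the planned Incucyte images at drug addition or irradiation and at the endpoint, in treated and control wells; or read a few control wells with CellTiter-Glo at time 0.
- Keep the endpoint-normalized IC50 and report a growth-rate-corrected response, such as GR above, beside it.

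In *Statistical analyses*: state that the association with clinical response will be examined under both scores and after accounting for untreated growth rate, for example as a covariate in the logistic regression already planned. Agreement would support a sensitivity signal; disagreement would point to growth.

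Cost: more image analysis or a few extra control wells per plate, with no new patients or tissue. Image area is only a proxy for viable cells. The corrected score is unstable in very slow lines and itself growth-dependent under pure killing, so it belongs beside IC50, not in its place.

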#### Evaluation of PDTO model relevance and identification of potential predictive biomarkers

##### Transcriptomic analysis

Total RNA will be extracted using the NucleoSpin miRNA kit (Macherey Nagel, Hoerdt). Libraries will be made by the Genomics Platform of the University of Lille with the QuantSeq 3’RNA Library Kitto allow polyA mRNA and lncRNA recovery. We will add ERCC spike-in for quality control. Library generation is initiated by oligo dT priming, from total RNA (200 ng). The primer already contains Illumina compatible linker sequences (Read 2). After first strand synthesis the RNA is degraded and second strand synthesis is initiated by random priming and a DNA polymerase. The random primer also contains 5′ Illumina compatible linker sequences (Read 1). At this step Unique Molecular Identifiers (UMIs) are introduced allowing the elimination of PCR duplicates during the analysis. After obtaining the double stranded cDNA library, the library is purified with magnetics beads and amplified. During the library amplification the barcodes and sequences required for cluster generation (index i7 in 3′ and index i5 in 5′) are introduced due to Illumina compatible linker sequences. Library is amplified with 14 PCR cycles. The final library is purified and deposed on High sensitivity DNA chip to be controlled on Agilent bioanalyzer 2100. The library concentration and the size distibution is checked. Each library is then pooled equimolarly and the final pool is also controlled on Agilent bioanalyzer 2100 and sequenced on NovaSeq 6000 (Illumina) with 100 cycles chemistry aiming to obtain a minimum of 20 M reads by sample.

To eliminate poor quality regions and poly(A) of the reads, we use the program fastp with quality score threshold of 20. We also remove reads shorter than 25 pb. The read alignments are performed using the program STAR with the genome reference human (GRCh38) and the reference gene annotations (Ensembl). The UMI (Unique Molecular Index) allowed to reduce errors and quantitative PCR bias are processed using fastp and umi-tools. Based on reads alignements, we counted the numbers of molecules by gene using FeatureCount. Others programs are performed for quality control as qualimap, fastp, FastQC and MultiQC. Statistical analysis is realized with the R/bioconductor package DESeq2.

##### Copy number variations analysis by low-pass whole genome sequencing

WGS will be performed using Illumina DNA PCR Free prep kit, starting with 500 ng of DNA. Library will be sequenced on a NovaSeq 6000 system aiming at 6x depth. Copy Number Analysis will be performed with HMMcopy and ichorCNA.

##### Transcriptome and CNV analysis

A preliminary analysis of intra reproducibility and differences between original tumors and PDTO assessed by PCA and unsupervised hierarchical clustering for each omic data after normalization will be done. For each sample we will plot barplot based on the normalized count of reads or number of aberration (CGH) for specific pathways to evaluate heterogeneity in each type of samples. Studied pathways will be defined with ingenuity pathways analysis (proliferation, apoptosis, etc). Each PDTO will be compared to original tumors data.

##### Targeted sequencing by NGS

“Mutational status (SNV, indels, CNV and translocations)” will be established on original tumor samples and PDTO derived from the primary tumor by targeted re-sequencing of a panel of 580 genes involved in cancer for DNA and of a panel of 57 genes implicated in protein fusion for RNA. DNA and RNA from samples will be extracted using QIAamp DNA kit (Qiagen) and NucleoSpin miRNA kit (Macherey Nagel, Hoerdt) respectively. DNA and RNA libraries sample preps and targeted enrichment will be performed using SureSelect XT HS2 DNA Reagent Kit (Agilent) and SureSelect XT HS2 RNA Reagent Kit (Agilent) respectively according to manufacturer’s instructions. Paired-end sequencing will be realized on a Nextseq500 sequencer from Illumina with a mean depth of coverage of 1000X. Bioinformatic analysis will be performed using an already developed pipeline. Briefly, duplicate reads merge, using unique molecular identifier, will be based on AGeNT (Agilent). The alignments will be based on BWA and GATK for BAM recalibration. Variant calling will be performed using Haplotype caller, Lofreq and OutLyzer. Finally, variant annotation will be realized with Alamut Batch and Annovar. The evaluation of copy number of targeted genes (Gain or Loss) will be evaluated using already published softwares such as ONCOCNV, CNVkit or current relevant tools.

### Statistical consideration

#### Sample size determination

To estimate the successful PDTO establishment rate, assumed around 60%, with a 95% confidence interval of 20% width, 89 tumor samples will be required. Anticipating 10% of non-assessable samples, it is planned to include 98 patients.

